**A61. Will participants be allocated to groups at random?**

☒ Yes ☐ No

*If yes, please give details of the intended method of randomisation:*

With each eligible participant identified, a coin will be tossed to decide which group they go into.

**A62. Please describe the methods of analysis (statistical or other appropriate methods, e.g. for qualitative research) by which the data will be evaluated to meet the study objectives.**

PART A: The Shapiro Wilk test will be used to assess the distribution of the data and to ensure no assumptions for statistical models are violated. Any data that violate the assumptions will be logarithmically transformed before statistical analysis. A two-way mixed design analysis of variance (ANOVA) will be used to analyse each muscle damage marker between exercise conditions and within time points. A two-way between-subjects ANOVA will be used to analyse each muscle damage marker between exercise conditions and between sexes. Independent t tests with Bonferroni corrections will be used to compare time-points between exercise conditions for all measures. Paired t tests will be used to detect any significant within-group changes between time points.

PART B: The Shapiro Wilk test will be used to assess the distribution of the data and to ensure no assumptions for statistical models are violated. Any data that violate the assumptions will be logarithmically transformed before statistical analysis. A two-way mixed design ANOVA will be used to analyse each muscle damage marker between dietary conditions (protein or placebo) and within time points. Independent t tests with Bonferroni corrections will be used to compare time-points between dietary conditions for all measures. Paired t tests will be used to detect any significant within-group changes between time points.

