**9. Is the study or any part of it being undertaken as an educational project?**

☒ Yes ☐ No

Please describe briefly the involvement of the student(s):

The primary researcher is a second year PhD student at Durham University. She will be responsible for participant recruitment, all data collection and storage, under the supervision of [name] and [name].

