**A13. Please summarise your design and methodology. It should be clear exactly what will happen to the research participant, how many times and in what order. Please complete this section in language comprehensible to the lay person. Do not simply reproduce or refer to the protocol. Further guidance is available in the guidance notes.**

OBJECTIVE 1/PART A: This study will employ a randomised parallel groups design, for which 40 healthy participants (20 males and 20 females) aged 18-35 years will be recruited. Prior to the first laboratory visit, prospective participants will have the opportunity to ask questions and gain further information about the study via a video/phone call with the

lead researcher. If willing to participate, participants will be asked to electronically sign a consent form. Female participants will be asked to record their menstrual cycle and inform the lead researcher at the onset of menses – this information will be used to arrange the time of the baseline assessments, as all measures will be conducted during the late follicular phase of the menstrual cycle.

For the first visit, which acts as a familiarisation session, participants will arrive at the laboratory in the morning and be screened for eligibility with a standard health and readiness to exercise questionnaire. Next, participants will be familiarised with the exercise equipment and demonstrated correct form. Then, participants' maximal strength will be estimated through a one repetition maximum (1RM) test on the leg press and leg extension machines. Approximately three days later, participants will return to the laboratory and a baseline assessment of body composition will be conducted using dual energy X-ray absorptiometry (DXA). Two whole-body DXA scans will be conducted in each participant (one immediately following the other after repositioning) to allow for the precision of DXA to be measured. The 1RM test will be repeated on the leg press and leg extension machines for confirmation of maximal strength. Participants will then be randomly assigned to either a low-load (30% 1RM) or high-load (80% 1RM) exercise condition, such that each group will have an equal number of males and females.

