**A59. What is the sample size for the research? How many participants/samples/data records do you plan to study in**

*total? If there is more than one group, please give further details below.*

Total UK sample size: 62

Total international sample size (including UK):

Total in European Economic Area:

*Further details:*

PART A: 20 males and 20 females

PART B: 22 females

**A60. How was the sample size decided upon?** *If a formal sample size calculation was used, indicate how this was done, giving sufficient information to justify and reproduce the calculation.*

PART A: A statistical power analysis was conducted. It was determined that a sample size of 8 per group was required to have 80% power to detect a between-group difference in muscle strength of 14%, when using a dependent t-test with a 0.05 two-sided significance level. A ~20% drop-out is anticipated, therefore, 10 males and 10 females in both groups will be recruited (n = 40 total).

PART B: A statistical power analysis was conducted. It was determined that a sample size of 9 per group was required to have 80% power to detect a between-group difference in muscle strength of 13%, when using a dependent t-test with a 0.05 two-sided significance level. A ~20% drop-out is anticipated, therefore, a total of 22 females will be recruited.

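### The coin toss in A61 cannot guarantee the equal numbers of men and women per load group that A13 and A60 state for Part A

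*Protocol*

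**What the plan says.** A61 asks for the intended method of randomisation. The whole answer is: "With each eligible participant identified, a coin will be tossed to decide which group they go into". It mentions no stratum, block or cap, and it does not say who tosses the coin or how the result is recorded.

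Two other answers describe the Part A groups as balanced by sex. A13 places assignment at visit 2, after the DXA scans and the repeat 1RM test, "such that each group will have an equal number of males and females". A60 derives the recruitment target from a requirement of 8 per group and about 20% drop-out, and concludes that "10 males and 10 females in both groups will be recruited". A59 gives the matching total: "PART A: 20 males and 20 females".

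For Part B, A13 and A60 state random assignment of 22 women to two groups, with 9 per group required. They promise no equal split.

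On roles, project filter question 9 says of the student who leads the study: "She will be responsible for participant recruitment, all data collection and storage". A27-1 and A29 add that the supervisors also recruit.

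**The concern.** Independent tosses and a fixed 10:10 split within each sex are two different allocation rules. The team cannot follow A61 as written and also be sure of the groups described in A13 and A60. In practice one must give way. Either the cells come out unequal, or someone departs from the coin to even them up, in a way the protocol does not describe.

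This matters because Objective 1 concerns sex differences in the response to load, so the four sex-by-load cells carry that comparison and each is planned at only 10. An ad hoc correction is the worse outcome. Once a cell is full, the remaining allocations in that sex are known beforehand, in a study where one person is responsible for recruitment and all data collection and no separate allocator is named.

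**Working it through.** **Inputs.** 20 men and 20 women in Part A (A59); required 8 per group and about 20% drop-out (A60); 22 women and required 9 per group in Part B (A60); one toss per participant (A61). Assumptions: a fair coin, and exactly 20 per sex allocated.

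**The plan's own figure.** 8 / (1 − 0.20) = 10, and 10 × 4 sex-by-load cells = 40, which matches A60. The inflation therefore implies that the 8 is meant per cell. This is a reading of A60, which says only per group. The 8 itself cannot be reproduced, because no standard deviation is given.

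**Chance of the planned split.** In each sex, the number allocated to one load is Binomial(20, 0.5).
- One sex: C(20,10)/2^20 = 184,756/1,048,576 = 0.176.
- Both sexes: 0.1762² = 0.031.
- Looser reading, in which men need only equal women within each load group: Σ[C(20,k)/2^20]² = C(40,20)/2^40 = 0.125.

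**Chance that a cell starts below 8.**
- One sex: 2 × P(X ≤ 7) = 2 × 137,980/1,048,576 = 0.263.
- At least one sex: 1 − (1 − 0.263)² = 0.457.

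**What this costs in precision.** The precision of a two-group comparison follows the harmonic mean, 2·n1·n2/(n1 + n2).

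| Split | Effective size per group |
|---|---|
| 10:10 | 10.0 |
| 7:13 | 2 × 91/20 = 9.1 |
| 6:14 | 2 × 84/20 = 8.4 |
| 5:15 | 2 × 75/20 = 7.5 |

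The effective size falls below 8 only at 5:15 or worse.
- One sex: 2 × P(X ≤ 5) = 2 × 21,700/1,048,576 = 0.0414.
- At least one sex: 1 − (1 − 0.0414)² = 0.081.

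These figures are before drop-out. The planned 10 leaves no reserve after it (10 × 0.8 = 8), and a 7:13 split would fall to 9.1 × 0.8 = 7.3.

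**If balance is forced by closing a cell at 10.** The expected number of remaining, predetermined allocations per sex is 2n·C(2n,n)/2^(2n) with n = 10, that is 20 × 0.1762 = 3.52. For both sexes this is 7.05 of 40. A simulation gave 3.53 per sex.

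**Part B, for scale.** With Binomial(22, 0.5), an arm starts below 9 with probability 2 × 600,370/4,194,304 = 0.286. The effective size falls below 9 only at 6:16 or worse (2 × 96/22 = 8.7), with probability 2 × 110,056/4,194,304 = 0.052.

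**With a list blocked to 20 per sex.** Both sexes split 10:10 and all four cells start at 10 with certainty, against 0.031 for the split and 0.543 for all cells reaching at least 8 under the coin.

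**The case against.** Simple randomisation is valid, and unequal cells cause no bias. The 46% counts only the smaller cell, and the 8% is the fairer measure of harm. The load comparisons in A62 that do not split by sex draw on all 40 participants, and the chance that a whole load group starts below 8 is about 0.00004. All of this stands. It limits the damage from imbalance but does not reconcile A61 with A13 and A60.

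Four stronger readings are tempting, and the documents do not support them.
- A reader might infer that the coin makes the planned design impossible. It does not: the split can occur by chance, and the fault is that nothing secures it.
- A reader might infer that the student tosses the coin and can steer allocation. No section says who tosses it, and a fair toss cannot be predicted. What the documents do show is a gap: no independent allocator, no record, and one person responsible for recruitment and all data collection.
- A reader might hold Part B to an 11:11 split. Part B states none, so only the requirement of 9 per group is relevant there.
- A reader might see A61 and A13 as conflicting on when allocation happens. Eligibility screening at visit 1 followed by assignment at visit 2 fits both.

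That strength and soreness measures depend on effort and assessor is a matter of blinding, which a better allocation list does not solve.

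**Conclusion.** The contradiction holds for Part A: the method stated in A61 does not secure the groups stated in A13 and A60. It produces the planned 10:10 in both sexes with probability 3.1%, or 12.5% on the looser reading. Taking the 8 as per cell, some cell starts short with probability 46%, and the effective size of a within-sex comparison falls below 8 before drop-out in about 8%. Forcing the balance would make about 7 of 40 allocations known in advance to whoever keeps the tally. These results assume a fair coin and exactly 20 per sex.

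The lack of an independent allocator and of a record is a gap in the plan and no evidence of misuse. A61 is the question that asks for these details, so the matter is not one left to a statistical analysis plan. It should be settled before the first participant is allocated, because allocation cannot be repaired afterwards.

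**What to change.** Replace the coin in A61 with a computer-generated permuted-block list with varying block sizes, stratified by sex in Part A and blocked in Part B. Choose block sizes that add up to 20 per sex in Part A and to 22 in Part B, so that the balance is exact if recruitment is completed.

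A supervisor who takes no measurements should prepare and hold the list, in sequentially numbered sealed opaque envelopes. As A27-1 also lists the supervisors as recruiters, this should preferably be one who does not recruit. Each envelope is opened and logged at the assignment point already given in A13, after the visit 2 baseline measures. The visit schedule does not change.

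The cost is a few minutes to generate the list and fill the envelopes. The drawback is slight predictability towards the end of a block, which varying block sizes limit.

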Visit three will occur three weeks later. In between visits two and three, participants will be asked to record their habitual diet and activity for three days, which will be used to assess any between-group differences. For each subsequent assessment day, participants will be prescribed a standardised breakfast to consume at home 3 hours prior to attending the laboratory. Otherwise, participants will be instructed to consume their habitual diet and, during each laboratory visit, a 24-hour dietary recall will be conducted to assess any changes in dietary intake. Participants will be instructed to abstain from the use of non-steroidal anti-inflammatory drugs, strenuous exercise, engagement in massage or cryotherapy, and the consumption of alcohol, protein supplements, vitamin and mineral supplements, and ergogenic aids during the study period.

Upon arriving at the laboratory for the third visit (pre), a trained phlebotomist will collect a venous blood sample in three vacutainers; one containing a serum separator (8.5 mL); and two containing no reagent (10 mL) (28.5 mL total). Following blood collection, the participants' limb circumference of the thigh will be measured with a standard measuring tape and their limb range of motion will be assessed with a goniometer. Muscle soreness will be measured by use of a visual analogue scale (VAS) questionnaire while performing a standard bodyweight squat, and the pressure-pain threshold (PPT) test using a standard pressure algometer. Participants will then perform a single bout of resistance exercise at their allocated load intensity, firstly on the leg press and secondly, on the leg extension, separated by five-minutes rest. The exercise protocol will consist of a warm-up set (10 repetitions at 50% of the participants pre-established 1RM), followed by three sets performed to volitional failure (when a full repetition can no longer be completed) at either 30% or 80% 1RM. Two-minutes of rest will be awarded between each set of exercise and the participants will be verbally encouraged throughout.

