Immediately following the exercise bout (post), another venous blood sample will be taken (3 x 8.5-10 mL) and the measures of limb circumference, range of motion, and muscle soreness will be repeated. Then, participants will be provided a dairy yoghurt containing 20 g of milk protein to stimulate muscle repair and growth. These four measures (excluding protein consumption) will be repeated during the morning of visits four (+24 h), five (+48 h), six (+72 h), and seven (+168 h). Also, during visits six and seven, the 1RM strength test will be repeated on the leg press and leg extension. Over the experimental period, a total of 171 mL of blood will be collected from each participant. This is the equivalent of ~34 teaspoons and is a common amount obtained during exercise physiology research. The blood samples will be used to analyse serum concentrations of creatine kinase, myoglobin (markers of muscle damage), C-reactive protein, and interleukin-6 (markers of inflammation).

**OBJECTIVE 2/PART B:** This study will employ a randomised parallel groups design, for which 22 healthy females aged 18-35 years will be recruited. Prior to the first laboratory visit, prospective participants will have the opportunity to ask questions and gain further information about the study via a video/phone call with the lead researcher. If willing to participate, participants will be asked to electronically sign a consent form. Participants will be asked to record their menstrual cycle and inform the lead researcher at the onset of menses – this information will be used to arrange the time of the baseline assessments, as all measures will be conducted during the late follicular phase of the menstrual cycle.

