#### 4. RISKS AND ETHICAL ISSUES

#### RESEARCH PARTICIPANTS

**A17-1. Please list the principal inclusion criteria (list the most important, max 5000 characters).**

Males and females (PART A)  
Females-only (PART B)

All other inclusion criteria apply to PART A and PART B:

Aged 18-35 years

BMI 18.5 -25.0 kg/m^2

Untrained in resistance exercise

No known chronic disease or current acute illness

No current or recent (past 3 months) musculoskeletal injury

No frequent use (2x per week for past month) of non-steroidal anti-inflammatory drugs and compliant to abstain from use during experimental period

No recent or current engagement in massage or cryotherapy and compliant to abstain from use during experimental period

No current use of protein or antioxidant supplements

Females will be eumenorrheic >12 months

Absence of pregnancy and breast-feeding

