**A57. What is the primary outcome measure for the study?**

Exercise-induced changes in markers of muscle damage

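### The rule to log-transform whatever fails Shapiro-Wilk cannot be carried out for soreness scores of zero, and it lets a noisy test choose each marker's scale

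*Protocol*

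**What the plan says.** Section A62 gives Parts A and B the same two-step rule. First: "The Shapiro Wilk test will be used to assess the distribution of the data and to ensure no assumptions for statistical models are violated". Second: "Any data that violate the assumptions will be logarithmically transformed before statistical analysis". The rule covers every measure. It names no exception, offset or alternative method, gives no significance level for the test, and does not say whether raw values, separate group-by-visit cells or residuals are tested.

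Among the measures is soreness. Section A13 states, for both parts: "Muscle soreness will be measured by use of a visual analogue scale (VAS) questionnaire while performing a standard bodyweight squat". It is scored on arrival at visit three before exercise, directly afterwards, and at 24, 48, 72 and 168 hours. Participants must have "No current or recent (past 3 months) musculoskeletal injury" (A17-1) and are told to avoid strenuous exercise (A13).

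Section A57 names the primary outcome as "Exercise-induced changes in markers of muscle damage". For Part A, A62 adds an analysis with no time factor: "A two-way between-subjects ANOVA will be used to analyse each muscle damage marker between exercise conditions and between sexes".

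**The concern.** A log exists only for positive numbers. Unlike an enzyme concentration, a pre-exercise soreness score in someone rested and uninjured may well be exactly zero. A score bunched at its floor is also prone to fail a normality test. The measure most exposed to the rule is therefore the one on which the rule cannot be carried out. The analyst would have to drop the zeros or add a constant, and A62 supports neither. Without a pre-exercise value, that person also leaves a complete-case mixed ANOVA.

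The second issue is who chooses the scale. A logged marker is compared between groups as a ratio and an unlogged one as a difference. Under A62 that choice follows from a test on the trial's own data, at group sizes where the test is weak. Two analysts could follow A62 and report different quantities for the same marker.

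**Working it through.** The protocol gives no figure for this rule, so there is nothing of its own to reproduce.

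**Inputs from the protocol.** A60 gives 8 to 10 per sex-by-load cell in Part A, hence 16 to 20 per load. For Part B it gives 9 per group required and 22 recruited, about 11 per group. A13 gives six time points.

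**Assumptions, because the protocol is silent.** The VAS starts at 0; a proportion q of people score 0 at a visit; Shapiro-Wilk is run at 5%.

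**1. Will there be zeros?** The chance of at least one zero among n people is 1 − (1 − q)^n. For n = 20:
- q = 5%: 1 − 0.95^20 = 64%
- q = 10%: 1 − 0.90^20 = 88%
- q = 50%: close to 100%

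For Part B with n = 22 and q = 10%, it is 90%.

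**2. Will such scores fail the test?** In simulated samples of 10, Shapiro-Wilk rejected in 41%, 81% and 98% of samples when 30%, 50% and 70% of people scored 0. The figures depend on the shape assumed for the non-zero scores: with exponential non-zero scores, the rate at 50% zeros was 93%. With few zeros the test may pass and the problem does not arise.

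**3. Is an added constant harmless?** Take ln(x + c). For a person rising from 0 to 40 the change is ln(40 + c) − ln(c); for a person rising from 2 to 40 it is ln(40 + c) − ln(2 + c).

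| c | 0 to 40 | 2 to 40 | gap |
|---|---|---|---|
| 0.01 | 8.29 | 2.99 | 5.30 |
| 0.1 | 5.99 | 2.95 | 3.04 |
| 1 | 3.71 | 2.61 | 1.10 |
| 10 | 1.61 | 1.43 | 0.18 |

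Two people with nearly the same experience differ by 5.30 or by 0.18 log units, depending on a constant that nobody has specified.

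**4. Change scores, if these are what is analysed.** Suppose changes are normal with a mean one SD above zero. Then 16% are zero or negative, and the chance of at least one among 20 people is 1 − (1 − 0.159)^20 = 97%. For strength and range of motion, where A12 expects losses, negative changes would be the rule.

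**5. How reliable is the test as a gate?** Share of truly lognormal samples that Shapiro-Wilk rejects (4,000 simulated samples per entry):

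| n | log-SD 0.5 | log-SD 0.8 | log-SD 1.0 |
|---|---|---|---|
| 8 | 19% | 37% | 48% |
| 9 | 22% | 39% | 54% |
| 10 | 23% | 46% | 60% |
| 11 | 29% | 51% | 67% |
| 16 | 42% | 73% | 85% |
| 20 | 51% | 85% | 94% |

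At the size of a Part B group or a sex-by-load cell, moderate skew is missed in about 71–81% of samples. At the 16 to 20 per load of Part A's load-by-time analysis the test does better, and for strong skew it does well.

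**6. Does the gate distort inference for positive markers?** Simulated rule: test each group, log both if either fails, then an independent t-test. Type I error lay between 4.6% and 6.0% across the settings run. Power for a ratio effect at n = 10 and log-SD 0.8 was 78.1%, against 77.6% when the log was always taken.

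**The case against.** Several replies have force.

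- **Negative changes.** A reader might infer from A57 that signed changes are analysed, so that the rule breaks for most markers. The text does not require this. The mixed ANOVA can be read as using the value at each visit, with change appearing as the time effect. Visit values of strength, range of motion, circumference, pain threshold and the blood markers are positive, so their logs exist. The load-by-sex ANOVA needs one value per person, but A62 does not say whether that is a change or a single time point. This part stands only conditionally.
- **Raw data or residuals.** A reader might infer that raw values are tested, so that real group, sex or time differences show up as non-normality. A62 also ties the test to model assumptions, which could mean residuals. The documents do not settle it.
- **False alarms.** Over 12 group-by-visit cells of normal data, 1 − 0.95^12 = 46% would show at least one false violation. That assumes cell-by-cell testing and independent cells, whereas six visits come from the same people. I do not rely on it.
- **Actual harm.** For positive markers in a two-group comparison, step 6 shows little. It does not cover zeros, repeated measures or the change in the reported quantity.
- **A matter for the analysis plan.** Offsets and test levels are commonly left there, and A54 mentions a statistical analysis plan. But A62 does not leave the transformation open. It states a rule without exceptions, and a later plan could cure it only by departing from that text.

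The zeros themselves rest on an assumption, since the VAS range and anchors are not stated. Soreness also has a second measure, pain threshold, and strength, on which the sample size rests, is unaffected by the zero problem.

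**Conclusion.** The main point holds for VAS soreness in both parts: as written, A62 leads to an undefined step whenever the score fails the test and someone has scored zero. This assumes a scale starting at 0 and a fair share of zero scores. At 50% zeros and n = 10, failure occurs in about 81–93% of samples; at 30% zeros, in about 41% under one assumed shape. Any patch by constant or deletion would change the result. The same applies to change scores if these are analysed, but not if visit values are used.

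The secondary point, that a weak test chooses between differences and ratios, holds mainly for Part B and the sex-by-load cells and for moderate skew. It concerns what is reported and whether it can be reproduced. The simulations do not support a claim of materially inflated type I error or lost power for positive markers. The sample size is not affected. The rule should be changed before analysis, though it does not threaten the trial as a whole.

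**What to change.** In A62, for both parts, replace the test-then-log rule by a scale fixed in advance for each marker:

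- creatine kinase, myoglobin, C-reactive protein and interleukin-6: log scale at all time points, reported as ratios;
- strength, range of motion, thigh circumference and pain threshold: original scale;
- VAS soreness: not log-transformed, with a rank-based or permutation comparison of groups as the check.

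Judge assumptions on model residuals instead of using Shapiro-Wilk as a gate. State in the same place whether the load-by-sex ANOVA uses a change or a single time point.

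The cost is wording and one small extra analysis for soreness. Visits, measurements and sample size stay as they are. Always logging the blood markers cost no power against the gated rule in the comparison above.

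### Replacing Bonferroni with Holm in A62 would gain some power at individual time points for a one-line change; in Part A the pre-exercise comparison should also leave the family

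*Protocol*

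**What the plan says.** Section A62 plans between-group tests at individual times in both parts. For Part A: "Independent t tests with Bonferroni corrections will be used to compare time-points between exercise conditions for all measures". For Part B: "Independent t tests with Bonferroni corrections will be used to compare time-points between dietary conditions for all measures". Neither sentence gives the number of comparisons or leaves out a time point.

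Section A13 sets the times. The first is before exercise: "Upon arriving at the laboratory for the third visit (pre), a trained phlebotomist will collect a venous blood sample in three vacutainers". The second is directly after it: "Immediately following the exercise bout (post), another venous blood sample will be taken (3 x 8.5-10 mL"). The measures then "will be repeated during the morning of visits four (+24 h), five (+48 h), six (+72 h), and seven (+168 h"). That makes six times, five of them after exercise. Strength has fewer: "Also, during visits six and seven, the 1RM strength test will be repeated on the leg press and leg extension". Its baseline is taken at visits one and two.

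Randomisation takes place at visit two. In Part A the visit-three pre measures precede the exercise. In Part B the breakfast eaten at home three hours before each assessment visit contains the allocated product.

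The sample size in A60 rests on an unadjusted test, "when using a dependent t-test with a 0.05 two-sided significance level".

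**The concern.** Two features of A62 cost power without buying extra protection.

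The first is the procedure. Bonferroni holds every comparison to the strictest threshold. Holm relaxes the threshold step by step and still keeps the family-wise error at or below 0.05 under any dependence between the times.

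The second is the family. If all six times are tested in Part A, one test concerns values taken after randomisation but before any exercise. Nothing in the plan would make the load groups differ there except chance, so that test answers no study question.

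The course of recovery at individual times is what the study sets out to describe, and the groups are small. In Part A the comparison is between load conditions, with 20 recruited per condition and about 16 after 20% dropout (20 × 0.8 = 16). Part B has 11 per group and about 9 after dropout (11 × 0.8 = 8.8). A real difference at a given time would be missed more often than it needs to be.

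**Working it through.** **The plan's own figure.** A60 states that "a sample size of 8 per group was required to have 80% power to detect a between-group difference in muscle strength of 14"%, and 9 per group for 13% in Part B. No standard deviation is given, so neither can be reproduced. For Part A, 8 per group implies an SD of about 14/1.51 = 9.3 points for an independent test, or 14/1.16 = 12.1 for a paired one. Effect sizes below are therefore assumptions, chosen to lie close to 80% power at an unadjusted 0.05. The exact values for that are d = 1.41 with 9 per arm and d = 1.02 with 16.

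**Thresholds.**
- Bonferroni over six times: 0.05/6 = 0.00833 at every time.
- Bonferroni over five: 0.05/5 = 0.0100 at every time.
- Holm over five, from the smallest p-value up: 0.05/5 = 0.0100, 0.05/4 = 0.0125, 0.05/3 = 0.0167, 0.05/2 = 0.025, 0.05/1 = 0.05.

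Holm's strictest threshold equals Bonferroni's over the same five times and exceeds Bonferroni's over six. So Holm over five rejects every post-exercise hypothesis that either Bonferroni rule rejects. This is arithmetic and needs no assumption about distribution or correlation.

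**Power per comparison under Bonferroni.** Power is the probability that a noncentral t with 2n − 2 degrees of freedom and noncentrality d√(n/2) exceeds the critical value at 0.05/k. The noncentrality is 1.4 × √4.5 = 2.97 for 9 per arm, and 1.0 × √8 = 2.83 for 16 per arm.

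**Power under Holm.** This was simulated with two-sample t tests at correlated times (correlation 0.6). Entries are average power per truly affected post-exercise time.

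| Setting | Times that differ | Bonferroni over 6 | Bonferroni over 5 | Holm over 5 |
|---|---|---|---|---|
| 9 per arm, d = 1.4 | five | 50% | 53% | 65% |
| | three | 50% | 53% | 58% |
| | one | 51% | 54% | 54% |
| 16 per arm, d = 1.0 | five | 51% | 54% | 64% |
| | three | 51% | 54% | 58% |
| | one | 51% | 54% | 54% |

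Entries vary by about a point between runs. The table separates two effects. Dropping the pre comparison is worth about 3 points. Changing Bonferroni to Holm over the same five times is worth about 11 points if all five differ, about 4 if three differ, and nothing if one differs. No post-exercise rejection was lost in the simulation.

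**Strength, two post-exercise times.** With d set to give 80% power at unadjusted 0.05 and correlation 0.5 to 0.8, Bonferroni over two gives 69–70% per time. Holm over two gives 75–76% if both times differ and does not improve on Bonferroni if only one does. If the baseline were counted as a third comparison, the starting point would be 63–64%.

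**Family-wise error.** With no true difference anywhere, Holm over five gives about 4% at correlation 0.6 and at most 4.9% at zero correlation. Both are within 5%.

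**The case against.** The strongest reply is that Bonferroni is valid, pre-specified and conservative, so choosing another valid correction is a matter of taste. The first half stands: nothing in A62 inflates error. The second half does not, because over the same family Holm dominates and needs nothing more of the data.

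Four other points stand and limit the finding.

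- A reader might infer that the plan definitely tests the pre values. A62 does not say so; that is only its literal reading. A57 defines the primary outcome as changes induced by exercise. If changes from pre are compared, the family is already five and only the step from Bonferroni to Holm remains.
- A reader might take 50% to 65% as the size of the problem. That combines both changes and needs an equal, very large effect at all five times. No passage supports that, and strength, the only outcome with a power calculation, is measured after exercise at just two times.
- A reader might infer that the pre comparison can be dropped in Part B as well. The documents do not support this, because the visit-three pre measures follow the first intake of the allocated product.
- The two methods share a cap, not an actual error rate. With three of five times truly different (16 per arm, correlation 0.5), the family-wise error is 1.9% for Bonferroni over five and 3.3% for Holm. Holm spends allowance that Bonferroni leaves unused.

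Bonferroni also has simultaneous intervals that match its tests. Holm has no simple equivalent.

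**Conclusion.** This is a cheap improvement and does not correct an error. That Holm never rejects less than Bonferroni, under the same 0.05 cap per marker, holds without assumptions. The size depends on assumed standardised effects, an assumed common correlation of 0.6 and the number of times that truly differ: from no gain to about 11 points of average power per affected time over a family of five, plus about 3 points in Part A if pre is now counted. Holm does not restore the 80% of the sample-size calculation in any setting examined. Neither method controls error across the several markers.

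**What to change.** In A62, replace Bonferroni with Holm in both parts.

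- **Part A:** define the family, per marker, as post, +24, +48, +72 and +168 h, and as +72 and +168 h for strength. Report the pre values descriptively, without a test.
- **Part B:** state whether the pre comparison is in the family, note that the allocated product is taken at breakfast before that visit, and apply Holm to the family chosen. Strength is not measured at visit three, so this caveat does not affect it.

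The cost is one line per part, with no extra participants, visits or assumptions. The price is in the intervals: they stay unadjusted or at Bonferroni width and may occasionally disagree with the Holm tests. The plan should say which it will report.
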